##### Health-related quality of life

Quality of life will be measured with the German version of the Short Form Health Survey (SF-12) [50]. The SF-12 consists of 12 items and assesses eight domains: physical functioning, physical and emotional role functioning, body pain, general health, vitality, social functioning and mental health. Physical and mental health composite scores can be calculated and range from 0 to 100, with higher scores indicating a better wellbeing. Its psychometric properties are well established [51].

##### State of self-esteem

Changes in self-esteem will be measured with the revised German version of the State Self-Esteem Scale (SSES) [52]. The SSES-revised measures state of self-esteem at a given point in time, and consists of 15 items that can be assigned to the following three factors of self-esteem: performance self-esteem, social self-esteem and appearance self-esteem. Respondents have to indicate their agreement to different statements about themselves (for example, ‘I feel good about myself’) on a five-point scale ranging from 1 (not at all) to 5 (extremely). Higher scores indicate a higher self-esteem. The internal consistency is α = 0.80 for performance self-esteem and α = 0.83 for social and appearance self-esteem [52].

##### Subjective need for psychotherapy

Changes in the subjective need for psychotherapy will be assessed by five newly developed questions. Respondents indicate their agreement to different statements (for example, ‘I currently have a high need for psychotherapy’ or ‘I currently would be okay without individual psychotherapy’) on a four-point scale from 1 (disagree) to 4 (agree).

##### Psychotherapeutic process

For the evaluation of the therapeutic process in the group program patients evaluate each group session with a session questionnaire. The session questionnaire used is a modified version of the patient version of the Bern Post Session Report (BPSR 2000) [53], extended by group specific aspects. The Bern Post Session Report modified for groups (BPSR-G 2000) includes 26 items rated on a seven-point scale ranging from −3 (not at all) to +3 (exactly). The 11 scales cover session impacts (experiences of mastery, clarification, control, problem actualization and self-esteem), other common factors (therapeutic alliance and therapeutic progress), group specific factors (cohesion and alliance with group members) and global evaluation scales (session evaluation and group setting evaluation). The psychometric properties of the original BPSR 2000 are well established [53].

##### Acceptance of the treatment

In order to measure the acceptance of the group program, dropout rates will be assessed. The therapist will document treatment attendance and disturbances. After every group session patients can describe their like or dislike of the session on three open questions in the session questionnaire. Additionally, patients will be asked to evaluate the subjective relevance of the different group topics after the completion of treatment.

#### Covariates

##### Demographic measures

We will measure age, gender and socioeconomic status with standard single-item questions.

##### Coping with a chronic disease

Coping behavior will be measured with the Trier Scales of Coping with Disease (TSK) [54]. This self-report questionnaire determines five domains: rumination, social coping (seeking social integration), threat minimization (denial), seeking information and turning to religion. There are 37 items that assess the frequency of specific thoughts and actions in recent weeks that can occur in the process of coping with a disease, on a scale ranging from 1 (never) to 6 (very often). Sum scores can be calculated for every subscale and can be compared with standard values. Its psychometric properties are well established [55].

### Sample size calculation

The literature indicates moderate effect sizes for group psychotherapy in the target group: in a meta-analysis, an average pre to post effect size of *d* = 0.49 for group psychotherapy for somatic diseases was found [24]. Effect size for group treatment compared to wait-list control (over all patient groups) was also indicated as moderate [24]. Comparable studies examining group psychotherapy for chronically ill patients with comorbid depression using HADS score as the primary outcome indicate moderate to strong effect sizes: Schuster *et al*. [30] found a strong interaction effect (*d* = 0.89) from pretreatment to six months follow-up for their CBT group therapy (six sessions) for patients with coronary or orthopedic diseases and comorbid depression, anxiety or somatoform disorders in comparison to the usual treatment of the rehabilitation clinic. Hambridge *et al*. [29] found a moderate effect from pre to post-treatment (*d* = 0.57) of their CBT group program (six sessions) for patients with coronary artery disease and comorbid depression.

In order to detect a main group effect of *f* = 0.25 [56] when adjusting for baseline severity, we will need a total sample size of 128 participants. This sample size provides a power (1-β) of 0.8 and an alpha of 0.05. Sample size calculations were done with G*power 3 software [57].

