**Methods/Design:**

A randomized controlled trial will be conducted to evaluate the efficacy of a cognitive behavioral therapy (CBT) group program for patients with somatic diseases and depressive or adjustment disorders, compared to a wait-list control group. A total of 128 adults with any chronic somatic disease and comorbid depression or adjustment disorder will be recruited in our outpatient clinic, and will be randomly assigned to participate in the group program immediately after contacting the clinic (intervention group) or after a waiting period of four months (wait-list control group). Primary outcomes will be self-reported depressive and anxiety symptoms. Secondary outcomes will be self-reported psychological distress, changes in experience and behavior, health-related quality of life, state of self-esteem and subjective need for therapy. Assessments will take place at baseline, 10 weeks (post-treatment) and 18 weeks (follow-up) after randomization. Additionally, treatment acceptance and psychotherapeutic process will be assessed after each session.

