The following admission procedure is equivalent for both groups. Patients from both groups receive an appointment for an initial consultation within two weeks after the telephone screening. The initial consultation is conducted by the head of the outpatient clinic. If patients appear suitable for the study at the initial consultation, a research assistant will inform them about the study immediately after the consultation. Patients who are interested in participating will receive materials containing detailed information about the study’s content and procedures, and will be called within one week to schedule an appointment for a Structured Clinical Interview for DSM-IV Axis I Disorders (SCID-I) [39]. At the beginning of the SCID-I interview, we will inform participants about data security and that they may withdraw from the study at any time without any negative consequences (for example, without prolonging the waiting period for individual psychotherapy). Written informed consent will be obtained from all study participants. All SCID-I interviews will be conducted by trained clinicians and will be videotaped for quality assurance if patients give their written consent.

Patients who fulfill all inclusion criteria and none of the exclusion criteria will be randomly assigned to the study conditions. In order to guarantee a continuous group size in the STEpS group program, we decided to use block randomization with a block size of 20 and an allocation ratio of 1:1. The allocation sequence will be created by computer-generated random numbers, and will be carried out by a researcher who is not involved in the enrolment and allocation process. Staff involved in enrollment and allocation do not know the allocation sequence; we will use a sealed envelope system. Study participants will be informed about study exclusion or inclusion, allocation to study condition and further study procedures by telephone.

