### Statistical analyses

All analyses will be based on the initial treatment assignment (intention-to-treat). Missing data will be treated according to the recommendations of Hair *et al*. [58]. First, the extent of missing data will be determined; then, the level of randomness (missing at random, missing completely at random or missing not at random) will be diagnosed applying Little’s missing completely at random test and t-tests for independent variables. According to Cho and Leonhart [59], data missing completely at random is very unlikely in a rehabilitation research setting, so missing data will probably be imputed with a missing at random-capable method (for example, using multiple imputations).

We plan to use a between-group analyses of covariance (ANCOVA) with baseline scores of the outcome variables as covariates to adjust for baseline differences. With these, we compare differences in the main outcomes between the intervention and control group at post-treatment (T_2_) and follow-up (T_3_) time points. Alpha levels will be adjusted for multiple testing. Cohen’s *d* will be calculated to measure the effect sizes. All statistical analyses will be performed using IBM SPSS Statistics 20. If we fail to achieve the target sample size within the given time frame and resources of our study, we will use analyses of variance (ANOVA) instead. Due to randomization, group differences at baseline (T_1_) will be not likely. We will then test for an interaction effect between group and time from T_1_ to T_2_ and a main effect of group from T_2_ to T_3_.

Explorative analyses will be conducted to examine potential effect moderators (demographic variables and coping style, such as seeking social integration or seeking information). Interaction terms of potential moderator variables and treatment will be created and analyzed by linear regression.

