## Discussion

In this study protocol we describe the study design of a randomized wait-list controlled trial that evaluates the efficacy of a newly developed CBT group program for patients with somatic diseases and comorbid depressive or adjustment disorders, which shall be applied as a first-line treatment prior to individual outpatient therapy. We expect that study participants will benefit from the group program on a clinically significant level when compared with a wait-list control group. Moreover, we will examine the acceptance of the group program and the psychotherapeutic process during group participation.

This trial has some limitations. First, we are not sure if we will achieve the sample size and the power that is needed to calculate ANCOVAs; if not, we will use ANOVAs instead. Second, all outcomes are based on self-reported data. Complementary clinician-rated outcome measures would be beneficial, but cannot be performed due to related effort. With this in mind, we paid particular attention to choosing applied self-report measurements of primary and secondary outcomes that are well validated. Third, the study is designed as a long-term investigation with three measurement points, so missing data are to be considered. Due to the fact that the study participants are motivated to begin a therapy in our outpatient clinic, response rates are expected to be rather high. Nonetheless, missing data will occur and can increase the risk of bias. In order to minimize this risk, we will handle missing data according to the latest recommendations [58, 59].

This study also has several strengths. First, the study has a strong methodology, applying a randomized study design with a wait-list control group and a pretreatment, post-treatment and 18-week follow-up measurement point. The examined intervention was developed based on empirical evidence in a four-stage process and was tested in a pilot group. Applied outcome measurements are widely used and well-validated assessments. Inclusion and exclusion criteria are well proved using SCID-I diagnoses. Even further, inclusion and exclusion criteria are defined as naturalistically as possible, allowing a large spectrum of somatic and mental comorbidities to enhance external validity and keep the study sample comparable to routine patient care.

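### The 128 patients needed in the analysis are also the 128 to be recruited, so the stated power of 0.8 has no allowance for the missing data the protocol expects

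*Protocol article*

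**What the plan says.** The section Sample size calculation sets the target effect, "In order to detect a main group effect of *f* = 0.25 [56] when adjusting for baseline severity", and concludes that "we will need a total sample size of 128 participants". It adds: "This sample size provides a power (1-β) of 0.8 and an alpha of 0.05". The software was G*Power 3.

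The abstract (Methods/Design) uses the same figure for enrolment: "A total of 128 adults with any chronic somatic disease and comorbid depression or adjustment disorder will be recruited". These patients are then randomized with "an allocation ratio of 1:1" (Assessment of eligibility and randomization). Neither place mentions an allowance for loss or a larger recruitment figure.

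Under Statistical analyses the article plans ANCOVA adjusted for the baseline score at T2 and T3, by intention to treat. Missing values will probably be imputed by a method valid under missing at random, such as multiple imputation. The Discussion expects response to be good because participants want to start therapy at the clinic, but then concedes: "Nonetheless, missing data will occur and can increase the risk of bias". No rate is given.

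**The concern.** A power calculation returns the number of patients whose outcomes must be available for analysis. Here that number is reused, unchanged, as the number to enrol. The two can be equal only if every randomized patient returns the outcome questionnaire, or if the calculation holds some reserve. The article itself expects missing data and claims no reserve.

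The stated power would then be somewhat too high. A null result might be read as evidence against the group program with more assurance than the data allow.

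**Working it through.** **Inputs.** From Sample size calculation: f = 0.25 (d = 0.50 for two equal arms), described as the effect after baseline adjustment; alpha 0.05; power 0.8; N = 128. From Statistical analyses: ANCOVA with one covariate, the baseline score. From the randomization section: equal arms. The article does not state sidedness. An F test with one numerator degree of freedom corresponds to a two-sided test, and it reproduces the article's figure. A one-sided calculation by the normal approximation gives 100 and does not. Loss rates are my assumptions, because the article gives none.

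**Formula.** Power = P[F′(1, N − 3, λ) > F(0.95; 1, N − 3)], where F′ is the noncentral F distribution and λ = f² × N = 0.0625 × N.

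**Reproducing the plan's figure.** At N = 128, λ = 0.0625 × 128 = 8.0 and power is 0.8014. At N = 127 it is 0.7983, and at N = 126 it is 0.7951. The smallest N with power of at least 0.80 is therefore 128, as stated. Leaving out the covariate changes only the denominator degrees of freedom and gives 128 again (0.8015). The figure is right, and it contains no rounding reserve.

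**Power when 128 are randomized and some outcomes are lost** (complete cases, f as the adjusted effect, alpha 0.05):

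| Assumed loss | Analysed | λ | Power |
|---|---|---|---|
| 0% | 128 | 8.00 | 0.801 |
| 5% | 121 | 7.56 | 0.779 |
| 10% | 115 | 7.19 | 0.757 |
| 15% | 109 | 6.81 | 0.734 |
| 20% | 102 | 6.38 | 0.706 |

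At 20% loss the type II error is 1 − 0.706 = 0.294, against 0.199 with no loss.

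**The other reading of f.** If f = 0.25 were on the unadjusted scale, adjustment for a baseline score with correlation ρ to the outcome would give an effective f of 0.25 / √(1 − ρ²). With an assumed ρ of 0.5 this is 0.25 / √0.75 = 0.289. Power is then 0.90 at 128 and 0.82 at 102, that is, after 20% loss. With an assumed ρ of 0.4 it is 0.865 at 128 and 0.78 at 102.

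**The case against.** **Baseline adjustment may supply a hidden reserve.** None of the effect sizes cited in the sample size section is described as baseline-adjusted, and 128 results with or without the covariate. If f is really unadjusted, the trial could lose 20% and still exceed 0.8 at ρ = 0.5. A reader might infer that power of 0.8 is out of reach for this design, or that it holds only with no loss at all. The documents do not support so absolute a statement, because it depends on how f is read. What stands is that the article describes f as the effect with adjustment, which most naturally puts the gain inside f already, and that it states no correlation.

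**Intention to treat with imputation keeps all 128 in the analysis.** It keeps the rows but does not in general restore the information in unobserved outcomes. The baseline score and the other time point may recover part of it. The powers in the table are therefore approximate lower bounds for each loss rate, not predictions.

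**Loss may be small.** The article expects good response and gives a reason. At 5% loss the cost is only about two percentage points. A reader might also infer heavy loss from wholly postal follow-up, but Procedure of assessments says the intervention group receives its post-treatment forms in the last session, and baseline precedes randomization. Only T2 and T3 are exposed to loss after randomization.

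**The Discussion already doubts whether the sample size and power will be reached.** That concerns failing to recruit 128, not losing outcomes once 128 are enrolled.

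**Conclusion.** The point holds in a limited form. The arithmetic behind 128 is correct. The fault is that the minimum number to be analysed is also the recruitment number, with no allowance for missing data that the article says will occur.

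With f taken as the adjusted effect and alpha 0.05, power is about 0.78 to 0.71 for assumed losses of 5% to 20%, before any credit for imputation. The shortfall is minor at 5% and becomes material from about 10%. If f is unadjusted and the baseline-outcome correlation is near 0.5, there is no shortfall up to 20% loss, but the article states neither condition.

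The planned adjustment of alpha for multiple testing also bears on power. It is a separate issue and no part of this conclusion.

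**What to change.** Keep 128 randomized. In Sample size calculation, state the loss the investigators expect at T2 and give power for the number expected to be analysed in place of 0.8: for example, about 0.78 with 5% loss, falling to about 0.71 with 20%. The rate should be the investigators' own, since the article offers none.

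If credit for baseline adjustment is intended, say that f = 0.25 is unadjusted, give the assumed baseline-outcome correlation, and quote the resulting power after loss.

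The cost is a slightly less favourable figure in one sentence. No more patients are needed and the analysis does not change.

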### Study objective and research questions

This planned study aims to evaluate the efficacy of a CBT group program (STEpS) developed to provide immediate help before potential individual psychotherapy for patients with somatic diseases and comorbid depressive or adjustment disorders. We expect that self-reported depressive and anxiety symptoms assessed by the Hospital Anxiety and Depression Scale will be reduced to a greater extent in the intervention group compared to the wait-list control group. Furthermore, we hypothesize that the group difference in symptom severity can also be demonstrated two months after treatment, although the effect will be smaller. In addition, we expect that the intervention group will be superior compared to the wait-list control group in terms of self-reported psychological distress, changes in experience and behavior, health-related quality of life, state of self-esteem and subjective need for therapy. We also assume that the acceptance of treatment, assessed by attendance rates and self-reporting, is high. Session questionnaires should provide additional information about the psychotherapeutic process of the newly developed group therapy program.

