#### Primary outcomes

##### Anxiety and depression

Anxiety and depressive symptoms will be measured with the German version of the Hospital Anxiety and Depression Scale (HADS-D) [41]. The HADS-D has been developed for patients with somatic diseases and assesses two domains: depression and anxiety. Each subscale consists of seven items assessing the severity of anxiety and depressive symptoms within the last week on a scale from 0 to 3. The sum score for every subscale can range from 0 to 21. Subscale scores between 0 and 7 indicate no depression or anxiety, scores between 8 and 10 indicate possible depression or anxiety and scores of 11 or higher indicate clinical depression or anxiety. Both subscales are reliable (HADS-D Anxiety Scale: α = 0.83; HADS-D Depression Scale: α = 0.82) and valid measures of depression and anxiety severity [42].

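### The stated power of 0.8 holds for one unadjusted test at alpha 0.05, but the plan tests two primary scales at two time points with an adjusted alpha

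*Protocol article*

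**What the plan says.** - **Sizing.** The Sample size calculation reads: "In order to detect a main group effect of *f* = 0.25" and, continuing after a literature reference, "when adjusting for baseline severity, we will need a total sample size of 128 participants". It then adds: "This sample size provides a power (1-β) of 0.8 and an alpha of 0.05". One effect and one undivided alpha enter the calculation.
- **Primary outcomes.** The abstract states: "Primary outcomes will be self-reported depressive and anxiety symptoms". The section on anxiety and depression scores these as separate HADS-D subscales ("The sum score for every subscale can range from 0 to 21") and names no total score as the primary endpoint.
- **Testing.** The Statistical analyses section plans ANCOVAs, with the baseline score as covariate, comparing the arms on the main outcomes at post-treatment (T2) and at follow-up (T3). It adds: "Alpha levels will be adjusted for multiple testing". It gives no method and no number of tests.
- **Follow-up.** The Study objective and research questions section expects a group difference two months after treatment too, "although the effect will be smaller".
- **Allocation.** Randomization is 1:1, so 128 means 64 per arm.

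The article does not put either scale, or either time point, ahead of the other in the testing.

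**The concern.** The alpha in the power statement is not the alpha that the analysis section says will be used. Two scales at two time points give up to four primary comparisons, and adjusting alpha for them makes each harder to pass than the sizing assumed. The total of 128 has no reserve to absorb this, because it is the exact minimum for one test at 0.05.

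Type I error is not at stake: the planned adjustment protects it, and a positive result would stay valid. The risk is in reading a negative one. If one scale or time point misses significance, a reader who trusts the 0.8 may take this as evidence against a moderate effect. Under a Bonferroni split, a true effect of the planned size would be missed on any given test about 29% of the time with two tests (1 − 0.712) or 38% with four (1 − 0.616), rather than 20%.

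**Working it through.** **Inputs from the protocol article:** N = 128, 1:1 allocation, f = 0.25 (d = 2f = 0.5 for two equal groups), alpha 0.05, one baseline covariate.

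**Assumptions, because the article is silent:** the adjustment method; the size of the family (four tests, or two if only one time point or one scale counts); the correlation between tests; and f = 0.25 as the effect after baseline adjustment.

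**Step 1: reproduce the stated figure.** The ANCOVA group effect is an F test with 1 and 128 − 3 = 125 degrees of freedom. The noncentrality is λ = N·f² = 128 × 0.0625 = 8.0. Power = P(F′(1, 125, λ) > F critical).
- N = 128, alpha 0.05: power 0.801.
- N = 127, alpha 0.05: power 0.798.

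So 128 is the smallest total that reaches 0.80, for one test at undivided alpha.

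**Step 2: same N and effect, Bonferroni alpha.**

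| Family | Alpha per test | Power per test | N for 0.80 per test |
|---|---|---|---|
| 1 test | 0.05 | 0.801 | 128 |
| 2 tests | 0.05/2 = 0.025 | 0.712 | 155 (156 for equal arms) |
| 4 tests | 0.05/4 = 0.0125 | 0.616 | 182 |

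Sidak hardly differs: 0.713 for two tests and 0.619 for four.

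**Step 3: a less costly adjustment.** Holm was simulated with all effects equal to d = 0.5 and a common correlation between tests of 0 to 0.7. Average power per test was 0.77 to 0.78 for two tests and 0.71 to 0.74 for four. This used a normal approximation, which is slightly generous (it gives 0.807 rather than 0.801 for the single test), so exact values would be marginally lower.

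**Step 4: both scales required, each at 0.05, at one time point.** Treat the two test statistics as bivariate normal with mean √8 = 2.83 and critical value 1.96. Joint power is 0.687 at an assumed correlation of 0.4 and 0.738 at 0.8.

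**Step 5: follow-up.** The article expects a smaller effect at T3 but gives no size. For illustration only, f = 0.20 gives λ = 128 × 0.04 = 5.12 and power 0.61 at alpha 0.05, 0.50 at 0.025 and 0.40 at 0.0125.

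**The case against.** **The shortfall depends on choices that the article does not make.** This stands in part. Neither method nor family is named, and such detail is commonly left to a fuller document. A reader might infer that the trial's real power is 0.62 to 0.71. The documents do not support that: those are per-test figures under an assumed Bonferroni split, and 0.71 also needs a family of two, whereas two scales at two time points make four. Holm loses less. The chance of winning at least one test exceeds 0.80 (about 0.83 to 0.98 under Bonferroni in the same simulation). A fixed sequence would keep 0.80 for its first test. But the article neither defines power as at least one success nor sets an order, and it expects reductions in both depressive and anxiety symptoms.

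**Baseline adjustment may win the power back.** Taking d = 0.5 as an unadjusted effect also gives 64 per arm, and the cited effects of 0.49 and 0.57 are pre-to-post figures not described as baseline-adjusted. On that reading λ = 8/(1 − r²), where r is the baseline-outcome correlation. An r of about 0.43 restores 0.80 at alpha 0.025, and about 0.55 does so at 0.0125. This cannot be excluded, but it is the less natural reading: the sizing sentence ties f = 0.25 to the baseline-adjusted comparison, and no correlation is given.

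**The follow-up was not necessarily sized on the T2 effect.** This stands. A reader might infer that T3 borrowed the T2 effect, but the sizing names no time point, and one cited effect (d = 0.89) runs to six-month follow-up. What the article supports is narrower: one effect size is given, and a smaller effect is expected at T3.

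**The arithmetic is right.** This also stands. It would be wrong to call this a calculation error, since 128 reproduces exactly for the test described.

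**Conclusion.** The point holds as an inconsistency between sizing and analysis, and it should be fixed. The power of 0.8 is true of one unadjusted test of f = 0.25, while the same article plans adjusted tests of two unranked scales at two unranked time points.

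The direction is firm for each of the adjustments examined, provided f = 0.25 is the baseline-adjusted effect: every per-test figure falls below 0.80, as does the joint figure when both scales must succeed. The size is conditional. It runs from a small loss (Holm, two tests) to a loss of almost 0.19 (Bonferroni, four tests: 0.801 − 0.616). Power at T3 would be lower still if the effect there is smaller, as the article expects; by how much cannot be derived from it. Because type I error remains controlled, this affects how the power claim and any non-significant result are read, not the validity of a positive finding.

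**What to change.** In the Sample size calculation, state that 0.80 applies to one test at unadjusted alpha 0.05. Name the adjustment and the family of tests, and give the per-test power that follows: about 0.62 for Bonferroni over four tests, about 0.71 if the family is two, or the Holm range if Holm is used. Add that power at T3 will be lower if the effect there is smaller. This costs wording only; the stated power becomes less favourable.

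Alternatively, at the sponsor's choice and before the data are analysed, pre-specify an order for the four tests, each at 0.05 and each conditional on the one before. The 0.80 is then true of the first test. The costs are that later tests cannot be claimed if an earlier one fails, and that the order introduces a ranking of scales and time points that the article does not now contain. It would also change the confirmatory testing while the trial is running (first enrolment September 2013, recruitment still open in May 2015), so it should be documented with its date.

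Neither route needs extra patients.
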